**Fig 2 pone.0273290.g002:**
[figure not shown]
Functionalities of the Adhera MejoraCare solution. Left: Symptom’s monitoring. Center: Patient empowerment categories in the educational section. Right: Educational units included in the ‘‘How to protect from coronavirus” category.

An AI-driven algorithm will be used for selecting and delivering tailored messages based on the user’s profile and scientific evidence, following the integrated behavior change model "I-Change". This algorithm is based on the work of Hors-Fraile et al. [37], and it has been successfully clinically validated for promoting smoking cessation in a randomized clinical trial [38].

The mobile app included in this mHealth solution will be downloaded and installed like any other commercial app from Google Play. The participant will receive an email from the research team with instructions on how to install the application. Specifically, the download link and an individual access code will be provided. The code can only be used once, which ensure that only one device can be use which the specific code. In case that the participant changed the mobile device during the study they can request an additional code, and this change will be track down to prevent data lose.

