#### Control group

The WL group will not receive any intervention during the 1-year study period.

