#### Adhera® MejoraCare Digital Program adherence

The number of times the participant uses the mHealth solution will be recorded and tracked.

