### Analysis

First, descriptive statistics and normality assumptions will be examined. In case assumptions are met, t-tests for independent samples, ANOVAs, and chi-square analysis will be calculated to observe differences between groups at baseline in quantitative and categorical variables. In case normality assumptions are not met, robust t-test for independent samples and robust ANOVAs will be calculated [62]. Effect size will be quantified using Cohen’s d (d; [63]) or its robust equivalent (*d*_*R*_; [64]) when normality assumptions are not met, and robust estimations are employed. Independent-sample t-tests and chi-squared tests will be also performed to check that there are no significant differences in sociodemographic characteristics of the participants between groups that can act as confounding variables (i.e., age, gender, year and CD diagnosis).

Then, the multivariate normality assumption on the primary and secondary outcome measures will be tested before computing the linear mixed models. If the assumption is met, linear mixed models will be performed for each dependent variable, considering temporal moments as an intra-group factor and condition as an inter-group factor, using the False Discovery Rate (FDR) adjustments for post-hoc multiple comparisons. Otherwise, their mixed robust equivalents will be calculated [62].

In addition, multiple hierarchical regression models will be used to identify possible predictors of evolution in the primary and secondary measures. In particular, it is expected that characteristics as the gender, age, the CD, and user’s technological profile will act as predictor for the level of adherence to Adhera® MejoraCare Digital Program intervention, and the change in quality of life, self-efficacy, health empowerment, and anxiety and depression symptomatology. Finally, moderation analyses will be performed to test whether the gender, age, the CD, user’s technological profile and level of adherence moderate the intervention’s effect on quality of life, self-efficacy, health empowerment, and anxiety and depression symptomatology. These analyses will be performed using the macro PROCESS (version 4.0, https://processmacro.org/). The conditional effects of condition on the dependent variables at medium (the mean), low (−1 SD), and high (+1 SD) levels of the moderator variables will be examined with the “pick-a-point approach”.

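### Adherence cannot be tested as a moderator of the intervention effect, because app use exists only in the intervention arm; the defect is confined to this one secondary analysis

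*Protocol article*

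**What the plan says.** All references are to the protocol article.

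- **Analysis.** The last analyses listed are moderation analyses. They ask whether gender, age, the chronic disease, the user's "technological profile and level of adherence moderate the" effect of the intervention on quality of life, self-efficacy, health empowerment, and anxiety and depression symptoms. On software: "These analyses will be performed using the macro PROCESS". On reporting: "The conditional effects of condition on the dependent variables at medium (the mean), low", with the low and high points set one SD either side of the mean. This is worded for the moderators as a group, with no exception for adherence.
- **Adherence section.** The measure is defined in one sentence: "The number of times the participant uses the mHealth solution will be recorded and tracked". The regression plan in Analysis confirms what is meant, namely the "level of adherence to Adhera® MejoraCare Digital Program intervention".
- **Control group.** "The WL group will not receive any intervention during the 1-year study period".
- **Experimental group.** Access to the app is by invitation: "Specifically, the download link and an individual access code will be provided". Each code works once.

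No adherence measure is described for the waiting list, and no other way of handling adherence in the moderation model is given.

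**The concern.** Moderation asks whether the difference between arms changes with the level of a third variable. That requires the variable to take a range of values in both arms. Adherence to the app does not: in the waiting-list arm it is zero for everyone, or undefined. The question as posed therefore has no answer in these data.

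The practical risk is that software may drop the redundant term and still print coefficients. Those would compare participants who chose to use the app at a given rate with all controls. App use is observed after randomisation and is self-selected, so randomisation does not protect that comparison. Presenting it as moderation would give it a standing it does not have.

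**Working it through.** The plan states no figure on this point, so there is none to reproduce. The check is whether the planned model can be estimated.

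**Inputs**
- Condition C: 1 = program, 0 = waiting list (Research design).
- Adherence A: count of app uses (Adherence section). For controls it is 0 or missing (Control group).
- Per-arm sizes tried: 37 and 47 (Sample size) and 48 (Abstract). The counts were simulated, and the result does not depend on them.

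**Model**

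Y = b0 + b1·C + b2·A + b3·(C×A) + error. The effect of condition at adherence a is b1 + b3·a, so b3 must be estimable.

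**Controls coded 0**
- Controls: C×A = 0×0 = 0 = A.
- Program arm: C×A = 1×A = A.
- The product column therefore equals the adherence column for every participant, and the model reduces to Y = b0 + b1·C + (b2 + b3)·A. Only the sum b2 + b3 can be estimated.
- Centring does not help. With mean Ā, C×(A − Ā) = A − Ā·C = (A − Ā) + Ā − Ā·C, which is a combination of the other three columns.
- Numerical check at 37, 47 and 48 per arm: largest difference between C×A and A is 0; rank 3 of 4, centred or not.

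**Controls coded missing**
- Listwise deletion leaves only the program arm, where C = 1 throughout. C then duplicates the intercept, and C×A duplicates A.
- Numerical check: rank 2 of 4. Neither the effect of condition nor its interaction is estimable.

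**What any output would mean**
- If the redundant column is dropped under zero coding, every control sits at A = 0 and the adherence slope comes from the program arm alone.
- The 'effect at a' is then the fitted program-arm outcome at use level a minus the mean of all controls.
- The low reporting point also fails under this coding. With equal arms, program-arm mean m and SD s, the pooled mean is m/2 and the pooled variance is (m² + s²)/2 − m²/4 = m²/4 + s²/2. The pooled SD exceeds m/2 whenever s > 0, so mean − 1 SD is a negative number of uses.

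**Comparison cases**
- A moderator measured in both arms, such as age: rank 4 of 4, interaction estimable.
- Adherence within the program arm only (intercept and A): rank 2 of 2. The slope is estimable, as an association.

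**The case against.** The strongest reply concerns weight. Adherence is one of five moderators in the last analysis listed, and none of the four hypotheses in the Introduction concerns moderation by adherence. The mixed-model comparison on the EQ-5D-3L, the secondary outcomes and the sample size do not use it. All of that stands.

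A reader might also infer several stronger points that the document does not support:

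- **That the mean and ±1 SD do not exist for gender.** A 0/1 variable has both. With an even split the mean is 0.5 and the SD about 0.5, so the outer points fall on the two categories. A narrower wording point remains for chronic-disease diagnosis if it is analysed as an unordered variable with several categories, but the article does not say how it will be coded.
- **That the moderation tests need a multiplicity adjustment.** This is a separate question about exploratory tests. An analysis plan may settle it, and a familywise error figure for such tests would need an independence assumption that is implausible for correlated outcomes.
- **That the investigators will report the program as working better when used more.** The article proposes neither zero coding nor such a report. The risk is real, but it is not a stated intention.
- **That predicting adherence from baseline characteristics is equally flawed.** That regression can be answered within the intervention arm.

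An unseen analysis plan does not remove the core point. The article states an analysis that cannot answer its stated question, so a further document could only replace it.

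**Conclusion.** The point holds for adherence alone. As defined, its moderation of the intervention effect is not estimable: rank 3 of 4 with controls at zero, rank 2 of 4 with controls missing, whatever the sample size. Any result produced would be a non-randomised association within the intervention arm.

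This rests on two readings of the article: that adherence means app use and nothing else, and that no waiting-list participant uses the app. Stray use by a few controls would restore rank formally, but the interaction would then rest on those few people.

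It would be wrong to conclude that the primary analysis or the moderation plan as a whole fails. The other four moderators are participant characteristics recorded at screening in both arms, and their interactions can be estimated. This is a correction that should be made before analysis, of secondary importance.

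**What to change.** 1. In Analysis, delete adherence from the list of moderators, and so from the variables at whose "levels of the moderator variables will be examined with the" pick-a-point method.
2. Add a sentence stating that the association between number of app uses and outcome change will be described in the intervention arm only, as exploratory and non-causal.
3. Optional: if an effect among users is wanted, a complier-average effect with randomisation as the instrument could be added, provided its exclusion restriction is stated. That restriction is that assignment has no effect on anyone below the chosen use threshold. It is strained if lighter use also helps, and because participants are unblinded and outcomes are self-reported. The article gives no threshold, so one would have to be fixed beforehand. Correcting the error does not require this analysis.
4. Minor: if chronic-disease diagnosis enters as an unordered multi-category moderator, report the effect of condition by category rather than at the mean and ±1 SD.

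Items 1, 2 and 4 cost a few lines of text and a small within-arm analysis. No new data, visits or participants are needed.

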**Method:**

A two-arm randomized controlled trial will be carried out, with repeated measures (baseline, 1-month, 3-month, 6-month, and 12-month) under two conditions: Adhera® MejoraCare Digital Program or waiting list. The primary outcome is a change in the quality of life on the EuroQol 5-Dimensions 3-Levels Questionnaire (EQ-5D-3L). Other secondary outcomes, as the effect on anxiety and health empowerment, will be considered. All participants must be 18 years of age or older and meet the criteria for chronic disease. A total of 96 participants will be recruited (48 per arm).

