### Sample size

Sample size calculation was done using G*Power [24], based on the primary endpoint. Specifically, sample size was calculated for a mixed ANOVA design, with the between effects being the experimental condition (2 groups) and the within-effects being the different time points. As we were interested in the interaction between experimental group and time effect, 8 measurements were specified (2 groups x 4 time points). With a power of 80%, and an alpha level = .05, and an expected moderated effect size of d = .50 according to similar studies [25], the required sample size is 74 participants (37 per condition). Taking into account a potential dropout of 20% according to literature [26, 27], this study will recruit a total of 94 participants (47 per condition).

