We would like to mention some possible limitations. First, the possible presence of a high dropout or attrition rate by participants from the mHealth solution intervention condition [67]. Second, the results of this RCT should be interpreted with caution as they are limited to only a few specific groups of CDs. Future research with mHealth solutions should focus on increasing the sample size and performing in-depth analyses on a wide range of CDs to draw more robust and generalized conclusions. Third, implementing mHealth technologies in a LMIC will represent a major challenge for both researchers and users given the characteristics of the context (e.g., Internet connectivity issues, experience with technology). Finally, it is worth mentioning that this study only includes participants with an Android smartphone, thus limiting the recruitment of potential users with smartphones with different operating systems such as iOS.

In conclusion, this study’s results could help understand better how to offer self-care strategies to people with CD and shed evidence on the impact of mHealth solutions on the management of chronic medical conditions in a LMIC during the COVID-19 pandemic.

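### Predictors of change and moderation are assigned to one-row-per-person regressions, although the planned mixed model could estimate them from all observed visits; expected dropout makes this a modest, avoidable weakness in secondary analyses

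*Protocol article*

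**What the plan says.** The Analysis section of the protocol article uses two kinds of model on the same repeated measures.

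- **Main effects.** If multivariate normality holds, each outcome gets a linear mixed model, "considering temporal moments as an intra-group factor and condition as an inter-group factor". If not, robust mixed equivalents are used.
- **Predictors.** Hierarchical multiple regressions are planned for adherence and for change in quality of life and other measures. No visit is named for the change.
- **Moderation.** Gender, age, diagnosis, technological profile and adherence are to be tested as moderators of the intervention effect, with conditional effects reported at the moderator mean and one SD either side. On software: "These analyses will be performed using the macro PROCESS (version 4.0, https://processmacro.org".

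Two other places bear on this. The Sample size section allows for loss: "Taking into account a potential dropout of 20% according to literature". The Discussion and conclusion lists among possible limitations "the possible presence of a high dropout or attrition rate by participants from the mHealth solution intervention condition".

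**The concern.** A likelihood-based mixed model uses the visits a participant attended before leaving. A hierarchical regression or a PROCESS run has one outcome value per person, so anyone without a value at the chosen visit is left out unless it is imputed. The main effect and the conditional effects of condition could therefore come from different sets of participants, although readers will set them side by side.

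If people doing poorly early on are likelier to leave, and more of them leave the app arm, those who remain in that arm look better than the arm as a whole. The conditional effects then lean towards the intervention, although the earlier scores that would correct for this have been collected. One outcome per person also gives up any precision from analysing the four follow-ups together.

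**Working it through.** **The plan's own figure.** Taking the 74 (37 per arm) as given, 37 / (1 − 0.20) = 46.25, rounded up to 47 per arm, or 94. This matches the Sample size section. The Abstract says 96 (48 per arm); that discrepancy is a separate matter and changes little here.

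**People in a one-row regression without imputation.** At 12 months, 94 × 0.80 = 75.2, about 75 (96 × 0.80 = 76.8, about 77). At earlier visits the number depends on when people leave, which the plan does not say:

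| Timing of loss (assumed) | 1 mo | 3 mo | 6 mo | 12 mo |
|---|---|---|---|---|
| All before month 1 | 75 | 75 | 75 | 75 |
| Even | 89 | 85 | 80 | 75 |
| All after month 6 | 94 | 94 | 94 | 75 |

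**Rows in a mixed model with baseline as a response.** All 94 people contribute. Under even loss, 94 + 94 × (0.95 + 0.90 + 0.85 + 0.80) = 423 of 94 × 5 = 470 rows. The other two patterns give about 395 and 451.

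**Bias, by simulation.** From the plan: 47 per arm, 20% overall dropout, five assessments. Assumed: true effect 0.50 SD at the moderator mean; interaction 0.30 SD per SD; between-visit correlation 0.5 or 0.7; dropout after month 1, logistic in the 1-month score. The one-row analysis regresses the 12-month score on condition, moderator, their product and baseline. The comparator is a likelihood-type model using the observed follow-ups. Overstatement = (estimate − 0.50) / 0.50.

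| Dropout, app vs waiting list | Log-odds slope per SD | One-row effect at moderator mean | Overstatement |
|---|---|---|---|
| 20% vs 20% | 1.0 | 0.50 | none |
| 30% vs 10% | 0.5 | 0.52 | 4% |
| 30% vs 10% | 1.0 | 0.53–0.54 | 6–8% |
| 30% vs 10% | 1.5 | 0.55–0.56 | 10–12% |
| 35% vs 5% | 0.5 | 0.53–0.54 | 6–8% |
| 35% vs 5% | 1.0 | 0.56 | 12% |
| 35% vs 5% | 1.5 | 0.57–0.58 | 14–16% |

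The strongest settings tried reached 0.58–0.59, about 17%. The likelihood-type model gave about 0.50 throughout. With month 1 as the outcome the one-row estimate was 0.49–0.51. The interaction moved from 0.30 only to 0.28–0.30.

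**Bias against noise.** The sampling SD of the effect is 0.17–0.21. A bias of 0.04–0.06 is between 0.04/0.21 = 0.19 and 0.06/0.17 = 0.35 of a standard error; the largest, 0.09/0.17, is 0.53.

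**Precision.** At a single visit the two methods have nearly the same standard error. If moderation is constant over visits and the correlation is 0.5, the residual variance given baseline is 1 − 0.25 = 0.75 and the residual covariance 0.5 − 0.25 = 0.25. Averaging four visits gives a ratio of √[((0.75 + 3 × 0.25)/4) / 0.75] = 0.71, a standard error about 29% smaller with complete data.

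**The case against.** The article states no complete-case rule, and missing-data handling for secondary analyses is often left to an analysis plan, which is not shown. This stands in part: the exclusion is the default consequence of the named tools, and imputation is not ruled out. But the choice of tool is stated, and imputation alone would not make these regressions use the follow-ups jointly.

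Several stronger readings are tempting, and the documents do not support them.

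- **That a dropout's change can never be scored.** No visit is named. Someone lost after month 1 still has a 1-month change, and the first hypothesis in the Introduction places the effect at 1 month.
- **That the main model always keeps partial series.** This is assured only if normality is met. How the robust fallback treats incomplete cases is not stated.
- **That the plan predicts heavier loss in the app arm.** The Discussion calls high attrition there possible, with no rate and no comparison with the waiting list. The splits above are assumptions, and with equal dropout the bias in the effect disappears.
- **That every predictor model is affected.** Adherence as an outcome comes from recorded app use and needs no follow-up questionnaire.
- **That moving everything into the mixed model costs nothing.** The waiting list receives no intervention for the year, so condition × adherence cannot be estimated in any model. For the five eligible diagnoses over five time points, the three-way term needs (5 − 1) × (2 − 1) × (5 − 1) = 16 parameters in about 94 people.

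**Conclusion.** The point holds as a modest weakness in secondary analyses. The plan specifies a model that can use every observed visit, then switches to tools that, without imputation, drop about 19 of 94 participants (94 − 75) at month 12 and do not analyse the follow-ups jointly. If dropout depends on earlier scores and is heavier in the app arm, conditional effects at a later visit are overstated by about 8–12% at a log-odds slope of 1 per SD (0.54 and 0.56 against 0.50), and by up to about 17% under stronger assumptions.

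Only the 20% comes from the documents; the arm split, slope, correlation and effect sizes are assumed. A reader might infer that the trial's main result is biased. It is not affected by this point, and the moderation term itself is little affected.

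**What to change.** In the Analysis section:

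1. For the baseline moderators (gender, age, diagnosis, technological profile), add condition × moderator to the mixed model already planned for each outcome, acting on the follow-up visits. Add condition × time × moderator only where the sample supports it, which for diagnosis is doubtful.
2. Include all observed visits of all randomised participants, and take the conditional effects at the same moderator values from this model.
3. Model predictors of change as predictor × time terms in the same model.
4. Keep PROCESS on completers as a sensitivity analysis, with the outcome visit named.
5. Remove adherence as a moderator of condition. The model with adherence as an outcome can stay as it is.

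The cost is a change of wording and a little programming, with no new data or participants. The downsides are more model terms and reliance on data being missing at random given the observed visits. The gain is assured only where the likelihood-based model is used, so the text should also say how the robust fallback treats incomplete series.

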The general practitioners and specialists participating in the study will identify patients belonging to the high-risk group for CDs. Once identified, the physicians will make a face-to-face appointment with the potential candidates to explain the conditions of participation in the research study. Those interested in participating will sign the informed consent form and complete a brief questionnaire to verify compliance with the inclusion criteria: men and women; 18 years and older; CD diagnosis (i.e., cardiovascular disease, chronic obstructive pulmonary disease, diabetes, hypertension, and cancer); no severe psychiatric comorbidities (i.e., substance dependence, bipolar affective disorder, obsessive compulsive disorder, psychotic illness); and own an Android smartphone. Physicians participating in the study will have access to the patient’s medical history to check for the presence of a diagnosis of mental illness and the presence of severe psychiatric comorbidity. Subsequently, those who meet the criteria for participation in the study will complete the measures corresponding to the baseline through the *LimeSurvey* platform via a link that will be sent to the participant’s email address. Afterwards, participants will be randomized to one of the two conditions (intervention or control). An independent researcher from Valencia University will generate a permuted block randomization with fixed and concealed block length (20 participants per block), and with an allocation ratio of 1:1, using a computerized random number generator (Random Allocation Software 2.0 [30]). For methodological reasons, participants will not be blind to the condition. All patients will be assessed at 1-, 3-, 6- and 12-months from the time of randomization via the *LimeSurvey* platform. Fig 1 shows SPIRIT flow diagram of the study.

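### The mean and ±1 SD probing rule covers every listed moderator, but chronic disease diagnosis is an unordered category with no mean or SD, and for gender the probe points are not real groups

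*Protocol article*

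**What the plan says.** The last paragraph of the Analysis section states that "moderation analyses will be performed to test whether the gender, age, the CD, user’s technological profile and level of adherence moderate the intervention’s effect". The outcomes named there are the primary one (quality of life) and four others: self-efficacy, empowerment, anxiety and depression. On software it says "These analyses will be performed using the macro PROCESS (version 4.0", and no coding or option for categorical moderators is given. The paragraph closes with the probing rule, a pick-a-point method that reads the effect of condition at three points: the sample mean, one SD below it and one SD above it. Its key words are "high (+1 SD) levels of the moderator variables will be examined". That rule is written for the moderators as a set.

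Two of the five are categorical. The eligibility section (Study population, recruitment, and eligibility criteria) defines "CD diagnosis (i.e., cardiovascular disease, chronic obstructive pulmonary disease, diabetes, hypertension, and cancer" and admits "men and women; 18 years and older". The five diagnoses have no order.

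**The concern.** A mean and an SD describe a quantity. For CD, the rule can be carried out only if the diagnoses are numbered and the number is used as a score. The interaction is then a straight line through an invented ordering, and a point one SD above the mean is a place on that line, not a group of patients. A different numbering gives a different slope, a different test and different conditional effects from the same data.

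For gender the problem is smaller. A two-level moderator has only one contrast, so the interaction test is sound. The mean and ±1 SD points, however, fall between or beyond the two codes.

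At stake is a stated question in a trial that pools five diseases: whether the program works differently by diagnosis. Left as written, the sentence either yields a CD result that depends on labelling, or leaves the analyst to depart from the rule after the data are seen.

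**Working it through.** The document gives no figure on this point, so there is none to reproduce. The check applies the stated rule to the two categorical moderators. The diagnosis effects, diagnosis shares and gender split are not in the document and are assumed.

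**CD**

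Assumed effects of condition in five diagnoses A to E: 0.8, 0.0, 0.5, 0.2 and −0.2 SD. Assumed shares: 25, 10, 25, 30 and 10%.

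Overall effect = 0.25×0.8 + 0.10×0.0 + 0.25×0.5 + 0.30×0.2 + 0.10×(−0.2) = 0.365 SD, whatever the numbering.

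With CD entered as a numeric score c, and arms balanced within diagnosis, the large-sample interaction slope is

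slope = Σ share × c × (effect − 0.365) / variance of c,

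and the effect at ±1 SD is 0.365 ± slope × SD of c.

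The products share × (effect − 0.365) for A to E are 0.10875, −0.0365, 0.03375, −0.0495 and −0.0565. Three numberings of the same patients:

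| Codes for A, B, C, D, E | Numerator | Variance of c | Slope | Effect at −1 SD | Effect at +1 SD |
|---|---|---|---|---|---|
| 1, 2, 3, 4, 5 | −0.3435 | 10.20 − 2.90² = 1.79 | −0.19 | 0.62 | 0.11 |
| 1, 4, 2, 3, 5 | −0.40075 | 8.05 − 2.55² = 1.5475 | −0.26 | 0.69 | 0.04 |
| 2, 3, 5, 1, 4 | 0.00125 | 10.05 − 2.75² = 2.4875 | 0.0005 | 0.364 | 0.366 |

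Over all 120 numberings the slope runs from −0.26 to +0.26 per code, and the effect at +1 SD from 0.04 to 0.69 SD. Part of that range is only a mirror image: reversing a numbering swaps low and high and leaves each diagnosis's fitted effect unchanged. The third row is not a mirror image of the others. There the same spread of true effects, from −0.2 to 0.8, shows as no moderation at all.

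A separate simulated data set of 94 participants, with other assumed effects (0.1, 0.8, 0.2, 0.6, 0.3) and the same shares, gave the same pattern: across the 120 numberings the effect at +1 SD ran from 0.03 to 0.85.

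**Gender**

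For a 0/1 code with share p of women and N participants, the mean is p and the SD is √(p(1−p)N/(N−1)). The Sample size section says "this study will recruit a total of 94 participants (47 per condition", so N = 94. The abstract's 96 gives the same points to two decimals, except at 50% women, where both totals give −0.003 and 1.003.

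| Assumed share of women | −1 SD | Mean | +1 SD |
|---|---|---|---|
| 40% | −0.09 | 0.40 | 0.89 |
| 50% | −0.003 | 0.50 | 1.003 |
| 60% | 0.11 | 0.60 | 1.09 |
| 80% | 0.40 | 0.80 | 1.20 |

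Only near an even split do the outer points fall on the two genders. In a simulated fit, changing the codes from 0/1 to 1/2 changed no estimate, and reversing them only exchanged low and high.

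**Precision of per-diagnosis effects**

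A diagnosis with an assumed 10% share of 94 has 9.4 people, or 4.7 per arm. The standard error of its treatment effect is √(1/4.7 + 1/4.7) = 0.65 SD. With the planned 20% dropout it is 3.76 per arm and √(2/3.76) = 0.73 SD.

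**The case against.** The strongest reply is that the sentence is loosely worded, not a plan to average diagnosis codes. It speaks of low, medium and high levels, which suits only quantitative moderators. Earlier in the same section the article separates quantitative from categorical variables and plans chi-squared tests for baseline balance. It nowhere says that CD enters as a number, and with indicator variables the dependence on numbering disappears. Indicator coding is also the kind of detail that a condensed article leaves to a fuller plan.

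Much of this stands. Numeric coding is implied by the probing rule, not stated, and the sentence may have been meant for the quantitative moderators. But the article does not leave the matter open: it states a rule for all the moderators it lists, and for CD that rule cannot be applied without a numeric score. That is a stated rule that misfires, not a missing detail.

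Two further replies also stand. Moderation by CD is in none of hypotheses a to d in the Introduction, and the Discussion leaves in-depth work across diseases to larger studies. All sizes above rest on assumed inputs.

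A reader might also infer that the gender results are arbitrary, that real differences would be reversed, or that the main result is at risk. The documents support none of these. The gender interaction test is valid and each gender's effect follows from the same fit. Reversing a numbering changes labels only; the real risk for CD is a distorted or masked pattern. The primary comparison does not use the moderation analyses.

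**Conclusion.** The point holds, at minor severity. For CD, the rule as written has no meaningful application, and following it literally makes the interaction and the conditional effects depend on numbering. That dependence arises when true effects differ between diagnoses, which is what the analysis is meant to detect. The range of 0.04 to 0.69 SD illustrates this under assumed effects and shares; it is not a forecast for this trial. It also presumes that CD would be scored numerically, which the article implies but does not say. For gender, only the reporting points are unsuitable, and near an even split even that has little effect. The sample size is unaffected.

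**What to change.** Amend the probing sentence in the Analysis section so that:

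- Probing at the mean and ±1 SD is limited to the quantitative moderators.
- The effect of condition is reported at the two observed values of gender.
- CD is entered as indicator variables (declared multicategorical in the software) with a joint interaction test. This has 4 degrees of freedom if the five diagnoses are mutually exclusive. The eligibility section does not say that they are; if a participant can have more than one, use one indicator per diagnosis.
- Per-diagnosis effects are given with confidence intervals and labelled exploratory, with small groups pooled by a rule set before the data are seen.

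The cost is a sentence or two and one software option. The joint CD test spends more degrees of freedom than a single slope, and with about 94 participants the per-diagnosis estimates will be imprecise, which the confidence intervals will show. No other figure in the protocol changes.
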